### **Perception of Blinding SWAT**

Blinding participants and assessors to the study allocation is considered key to the interpretation of the study results. Knowledge of allocation can have a substantial effect on patient-reported outcomes and clinical assessments.

This SWAT aims to evaluate how well blinding is achieved, both for participants and assessors. Participants will be asked which treatment they think they received as part of their follow-up questionnaires. Assessors will be asked the same at the clinical assessments. Attitudes to blinding and to perception of treatment allocation will be explored with participants in the focus groups as part of the pilot phase.

The SWAT will demonstrate the reliability of participant and clinical blinding methods and the validity of the results within a context of blinding. It will facilitate the monitoring of blinding at sites, highlighting where efforts may need to be improved.

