| Sponsor                         | University of Oxford
Joint Research Office
[name]
[name]
[name]                                                                                                                                                                                |                                                 |                                                    |
| Funder                          | National Institute of Health Research, Health Technology Assessment
NIHR Evaluation, Trials and Studies Coordinating Centre
University of Southampton
[name]
[name]
Southampton
[name]
[contact]
[name]                                                        |                                                 |                                                    |
| Study Design                    | Multi-centre, parallel, blinded (participant and assessor) two arm randomised controlled trial including economic analysis                                                                                                                                                                                                           |                                                 |                                                    |
| Study Participants              | Patients 18 and over presenting with a single unilateral digital nerve injury appropriate for surgical repair.                                                                                                                                                                                                                       |                                                 |                                                    |
| Sample Size                     | Randomised Trial: 478 participants, 239 in each treatment arm
Pilot phase focus groups: 4-8 participants in each group, 3-4 groups                                                                                                                                                                                                |                                                 |                                                    |

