| Planned Study Period            | 01 Oct 2019 – 30 Nov 2024
Total length of project: 62 months
Individual participant involvement: 12 months                                                                                                                                                                                                                     |                                                 |                                                    |
| Planned Recruitment period      | 01 Apr 2020 – 31 Mar 2022
(embedded pilot phase 9 months from start of recruitment)                                                                                                                                                                                                                                               |                                                 |                                                    |
| Intervention(s)                 | Digital nerve surgery with microsurgical sutures.                                                                                                                                                                                                                                                                                    |                                                 |                                                    |
| Comparator                      | Digital nerve surgery with realignment of nerve ends but no microsurgical sutures.                                                                                                                                                                                                                                                   |                                                 |                                                    |
|                                 | Objectives                                                                                                                                                                                                                                                                                                                           | Outcome Measures                                | Timepoint(s)                                       |

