## 7.1. Pilot Phase

Incorporated within the NEON study design is a recruitment pilot phase, which will involve up to 9 centres with a staggered initiation over a period of 9 months. The aim of the pilot is to assess the following criteria: recruitment rate; ability to maintain assessor and participant blinding; adherence to the randomised procedure and early retention rates. The initial 9 centres will be used as a basis for revising aspects of study conduct.

Screening forms containing eligibility, reasons for exclusion and patients declining to participate will be completed. Rates of consent withdrawal and compliance with the randomised allocation will also be recorded. Any obvious barriers to recruitment will be assessed at 9 months. The overall recruitment target for the pilot is 44 participants, based on one participant per site per month with staggered site initiation.

The study team and oversight committees will consider all aspects of study conduct and any new evidence as the study moves into the definitive phase. Based on how the above criteria are met, the study team and committees will consider whether substantial changes are needed, and ultimately consider the viability of the study as currently designed and funded. Specific examples of this are seen in Table 1. Major changes derived from pilot work will be discussed with the appropriate stakeholders.

**Table 1:** Success criteria within the pilot study

|                                                                                                           | Red                                                                                                   | Amber                                                                                                                                             | Green                                                                        |
|-----------------------------------------------------------------------------------------------------------|-------------------------------------------------------------------------------------------------------|---------------------------------------------------------------------------------------------------------------------------------------------------|------------------------------------------------------------------------------|

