| Adherence to randomised procedure                                                                  | 10 (23%)                                                                                              | 22 (50%)                                                                                                                                          | 38 (85%)                                                                     |
| Action                                                                                             | Consider screening log data and feedback from sites and discuss with TSC to consider stopping trial   | Consider screening log data and feedback from sites and discuss with TSC strategies for improvement and consider changes to processes             | Proceed to main trial – consider screening log data and feedback from sites. |

| Retention                                                          |                                                                                                       |                                                                                                                                                   |                       |
|--------------------------------------------------------------------|-------------------------------------------------------------------------------------------------------|---------------------------------------------------------------------------------------------------------------------------------------------------|-----------------------|
| PROMS collection and blinded assessment at 3 months         |                                                                                                       |                                                                                                                                                   |                       |
| (21 patients may reach 3 months follow up within the pilot) | 2 (10%)                                                                                               | 7 (33%)                                                                                                                                           | 11 (52%)              |

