### Focus Groups

Participant focus groups will explore the study pathway and attitudes towards randomisation and blinding. The challenges of the study will be discussed, and the results will be used to further refine recruitment procedures, study information presentation and delivery, and training for clinical and research teams at sites.

Participants who agree to be contacted will be invited to take part in focus groups as part of the pilot phase. The focus groups will be held at the Botnar Research Centre in Oxford in the first instance. If participants from other sites express significant interest, efforts will be made to organise groups locally. All focus groups will be audio recorded and transcribed by a professional transcribing firm routinely sourced by the University of Oxford and versed in dealing with patient data. A confidentiality agreement will be put in place and any identifying information appearing in focus group transcripts will be removed as soon as possible following transcription to minimise risk of participant identification. Audio files will be treated as identifying data and will be excluded from archiving and sharing.

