### **Unblinding**

Those in the clinical team and the central study team will not be blinded to the allocation, so no code break procedure for clinical care or safety reporting is needed. The central study team will discuss specifically with each site which techniques they will employ to ensure participant and staff blinding. In any case in which unblinding is needed, or in which it occurs accidentally, the study team will follow processes as per the OCTRU Standard Operating Procedures (SOPs).

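### Pilot focus groups leave room for blinded participants to compare guesses about their allocation at least three months before the 12-month primary outcome

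*Protocol*

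**What the plan says.** Two places in the protocol describe what the focus groups are for. Section 7.1, under Focus Groups, says: "Participant focus groups will explore the study pathway and attitudes towards randomisation and blinding". Section 8.5, under Perception of Blinding SWAT, goes one step further: "Attitudes to blinding and to perception of treatment allocation will be explored with participants in the focus groups as part of the pilot phase".

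On who attends, section 7.1 says: "Participants who agree to be contacted will be invited to take part in focus groups as part of the pilot phase". It sets no condition that they have finished follow-up. The synopsis gives the size ("Pilot phase focus groups: 4-8 participants in each group, 3-4 groups") and the timing of the pilot ("embedded pilot phase 9 months from start of recruitment"). Table 1 feeds focus-group input into the decision on whether and how to proceed, which ties the groups to the pilot.

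The primary outcome, I-HaND v2, is patient-reported. Section 8.10 places the primary endpoint at 12 months. Appendix A lists the participants' perception-of-treatment item at 12 months only. Section 8.5 treats blinding as central to reading the results and warns that knowing the allocation can materially alter patient-reported outcomes. It also accepts that participants under light or no sedation may pick up cues from equipment in theatre.

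**The concern.** Someone who noticed something in theatre may not know what it meant. A discussion with others who had the same operation, some with the nerve sutured and some without, gives a basis for comparison. If perception of allocation is on the agenda and no limit is stated, participants can compare cues and guesses while their primary outcome is still to come. The protocol itself identifies this kind of knowledge as a threat to patient-reported outcomes.

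Two results could be affected. One is the 12-month I-HaND of the attendees. The other is the blinding SWAT. Because Appendix A schedules the individual perception item only at 12 months, no attendee would have given an individual answer before the group. A confident answer at 12 months could then reflect imperfect blinding in theatre or the group discussion, and the two could not be told apart.

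**Working it through.** **Timing**
- Longest possible time since randomisation at the end of the pilot: 9 months (synopsis). Primary endpoint: 12 months (section 8.10).
- Time remaining for any attendee during the pilot: at least 12 − 9 = 3 months.
- Section 7.1 gives the pilot target ("The overall recruitment target for the pilot is 44 participants, based on one participant per site per month with staggered site initiation"), and Table 1 notes that "21 patients may reach 3 months follow up within the pilot". So 44 − 21 = 23 of 44 (52%) would be under 3 months from randomisation when the pilot ends, with more than 9 months left.
- Check of those counts, assuming one new site each month and one participant per site per month: 1 + 2 + … + 9 = 45 (protocol: 44), and 1 + 2 + … + 6 = 21 reaching 3 months (protocol: 21). The protocol's figures are coherent.

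**Would a group contain both arms?**
Treating 1:1 allocations as independent, the chance that a group of k includes both arms is 1 − 2 × 0.5^k.
- k = 4: 1 − 0.125 = 0.875.
- k = 8: 1 − 0.0078 = 0.992.

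Mixed groups are the likely case, though not a certain one.

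**How many people**
- Smallest: 3 × 4 = 12. Largest: 4 × 8 = 32.
- Share of all randomised: 12/478 = 2.5% to 32/478 = 6.7%.
- Share of the pilot target: 12/44 = 27% to 32/44 = 73%.

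**Size of the effect on the primary comparison**
The protocol's own sample size reproduces. With a difference of 7, SD 21, two-sided 5% and 90% power, the t-test solution is 190.1 per group, rounded up to 191. Then 382/0.80 = 477.5, rounded to 478.

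The documents do not say how far firmer guesses would move I-HaND, so the following range is an assumption: a change of 3 to 7 points in the between-arm difference among attendees, applying to every one of them.
- Trial-wide shift = (attendees/478) × change among attendees.
- Low end: 12/478 × 3 = 0.08 points.
- High end: 32/478 × 7 = 0.47 points.
- If all attendees returned data and only 382 were analysed: 12/382 × 3 = 0.09 to 32/382 × 7 = 0.59 points.

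For the 0.47-point shift, the standard error at 191 per group is 21 × √(2/191) = 2.15. If the shift worked against a true 7-point difference, power would fall from 90% to 86%. If there were no true difference, the two-sided type I error would rise from 5.0% to about 5.6%.

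**The case against.** The strongest reply is that the SWAT sentence concerns attitudes to perception of allocation, not each person's own guess. Section 7.1 lists only the pathway and attitudes to randomisation and blinding, and section 8.5 gives the own-guess question to the follow-up questionnaires. Read together, the intended discussion may already be close to what is proposed here. A topic guide outside the protocol may say so, and early learning about blinding is a stated aim of the pilot. All of this is fair. What remains is that the protocol's wording permits the comparison of guesses, states no limit on it, and fixes a time when every attendee's main outcome is outstanding.

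Several stronger readings are tempting and are not supported.
- *That the groups will unblind participants.* Attendees do not know their allocation, and nothing in the protocol provides for disclosing it. The route is inference, so the risk is firmer guesses.
- *That scars would give the arm away.* Both arms have exploration, washout and standard wound closure. Only the theatre cues have support in the text.
- *That the venue is itself a route.* Section 8.5 says "Those in the clinical team and the central study team will not be blinded to the allocation", and the first groups are to be held in Oxford. The protocol does not say who will facilitate, or that a facilitator would know or reveal allocations.
- *That most of the pilot's blinding data would be compromised.* The share is 27% to 73% of the pilot target, so this holds only towards the upper end.
- *That a missing sensitivity analysis is an error.* That belongs in the SAP, which is not shown. Nor is attendance untraceable, since section 15.6 provides vouchers and travel reimbursement for it.

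**Conclusion.** The point holds as a modest one. The protocol puts perception of allocation on the agenda of group discussions among blinded participants at least 3 months before their primary outcome, without limiting what may be compared. This sits awkwardly with the warning in the same section about the effect of knowing the allocation.

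The consequence for the primary result is probably small: 2.5% to 6.7% of participants exposed, and about 0.1 to 0.5 points against a 7-point target. That range rests on an assumed 3 to 7 point change in every attendee, and its upper end equals the full target difference, so it is generous. The primary conclusion is unlikely to turn on it. The effect on the blinding SWAT is confined to the attendees' own answers. It depends on Appendix A being right that the item is asked only at 12 months; section 8.5 speaks of follow-up questionnaires without giving times.

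This is a low-priority improvement, worth making because it is cheap and leaves the pilot's check on blinding intact.

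**What to change.** 1. State in section 8.5 (Perception of Blinding SWAT) and section 7.1 (Focus Groups) that, until a participant's 12-month outcomes are returned, group discussion is limited to the study pathway, the information given, and general attitudes to randomisation and blinding. Add that participants are not asked to share or compare which treatment they think they had.
2. Collect perceived allocation from attendees individually before the group. The existing item cannot serve as scheduled, because Appendix A places it at 12 months only. The schedule needs one added earlier item for attendees.
3. Flag attendance in the trial data, so that a sensitivity analysis of I-HaND and of the blinding SWAT can exclude attendees.

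The cost is a short protocol and topic-guide edit, one extra item, one data flag and one extra analysis. There are two drawbacks: slightly less group material on perceived allocation, and an early item that may itself prompt a guess.

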## **8.6. Description of study intervention(s), comparators and study procedures (clinical)**

### **Surgical Preparation**

The procedures will be undertaken as per NHS practice by specialist surgeons. They will be done either as a day case (vast majority) or as an inpatient, and will utilise either general or local anaesthesia as per clinical judgement.

Washout and exploration will be carried out in a sterile environment in an operating theatre as per standard practice. Exploration will include examination of the wound under anaesthesia with identification of all structures within the zone of injury, where applicable.

### **Surgery with microsurgical sutures**

After exploration and washout, participants allocated to sutures will have this performed using end-to-end epineural sutures using, in the majority of cases, 8.0 or 9.0 synthetic non-absorbable suture under magnification (microscope or loupe).

### **Surgery without microsurgical sutures**

After exploration and washout, participants allocated to no sutures will have the cut nerve ends realigned and laid back in-situ.

### **Completion of surgical procedure**

Any associated injuries, such as flexor tendon injury, will be repaired, and the wound will be closed as per standard care. Dressings will be applied as per surgeon preference, and will depend on the extent of the injury, subsequent dissection and other associated injuries.

This intervention is a one-off treatment. Any further treatments will be sought as per routine NHS pathways.

### **Post-intervention rehabilitation**

Simple (isolated) digital nerve injuries (without concomitant tendon or other tissue injury) are not routinely referred for hand therapy. For the purposes of this study, all participants with these simple injuries will be provided with a standardised advice sheet and a sensory relearning advice sheet, given out at discharge.

Participants with concomitant injuries will be referred to hand therapy for rehabilitation as per standard practice. Hand therapists will issue the same sensory relearning advice sheet when deemed safe for the participant to do the exercises without compromising tendon healing. Any hand therapy sessions will be logged at clinic visits.

## **8.7. Baseline Assessment**

It is not possible to collect pre-injury baseline data. Injury details will be collected as part of the operative assessment, rather than as a separate baseline data.

## **8.8. Operative Assessment**

At the time of surgery, the operating surgeon will confirm the diagnosis of a nerve laceration and the randomisation minimisation factors. Further details of the injury and procedure will be recorded. This will include adherence to the randomised allocation, the extent of concomitant injury repair needed and any complications.

## **8.9. Subsequent Visits**

Follow-up will involve clinical appointments at 3 and 12 months post randomisation (supplementary to routine care), and participant questionnaires at 6 weeks, 3, 6 and 12 months post randomisation.

### **8.9.1 Clinical appointments**

Current best evidence indicates that neurosensory recovery after this injury should be assessed using a variety of sensory tests, including touch threshold and spatial discrimination (21). These are recommended standardised tests for assessment of sensory function after nerve repair from the Swedish national quality registry for hand surgery ([www.hakir.se](http://www.hakir.se)) and the American Society of Hand Therapists Clinical Assessment Recommendations (22).

NEON clinical appointments are supplementary to standard care. They will be conducted by blinded research nurses or research therapists not involved in routine patient care. Blinded assessors will receive training on the standardised administration of measures through the provision of a manual and videos.

Further training workshops will be provided by the study team if deemed necessary following pilot review. The assessments should take approximately 30 minutes per participant and be conducted in a quiet environment, preferably an office or side room.

- Touch thresholds using Weinstein Enhanced Sensory Test (WEST) monofilaments.  
Assessors will follow a standardised protocol of randomised sequences to touch, or pretend to touch, the area impacted by the digital nerve injury 5 times with monofilaments. Doing this with different weighted filaments will allow the assessor to determine the lightest filament at which 4 out of 5 applications are correctly detected.
- Static two-point discrimination test (2PD) assessed with Dellon-Mackinnon DiskCriminator.  
The 2PD threshold will be determined by trials of 10 random applications of 1 or 2 points at different widths (between 2-30mm). The smallest distance at which participants identify 1 or 2 points correctly 7 out of 10 times will be recorded as the final threshold.
- Tactile gnosis using Shape/Texture Identification (STI) test  
Assessors will follow a standardised protocol, through which participants rely on tactile gnosis to identify three shapes (circle, square and hexagon) and three textures (sets of raised dots) fixed on three different discs. Participants work through 3 levels of smaller shapes and dots.
- Complications assessment  
Complications being reviewed include: neuroma, lack of sensitivity, hypersensitivity, cold intolerance, complex regional pain syndrome and flexor tendon re-rupture, stiffness and swelling.

